## Rationale for Current Trial

The purpose of this trial is to evaluate the effects of Rebif® 44 mcg subcutaneous (sc) three times a week (tiw) on a) remyelination/demyelination, b) lesion and brain volume, c) CNS iron deposition, and d) immune status in subjects with RRMS via several MRI techniques.

It has been shown in several phase II, III and IV clinical trials that Rebif® 44 mcg had a robust effect on the decrease of inflammatory MRI activity and clinical activity as measured by reduction of clinical relapses and slowing in progression of disability. The potential effect of Rebif® 44 mcg on remyelination is unknown. This study will address these important questions by using voxel-wise MTR dynamic mapping of lesions and NABT to examine the evolution of these measures over six months.

Iron is essential for cellular physiology and normal metabolism of the body. It is required by all living cells due to its role in tissue formation, angiogenesis, oxygen transport, electron transfer, neurotransmitter synthesis, and myelin production; however, excess iron can be harmful (36). In excess, it contributes to a number of neurodegenerative processes because free ferrous (Fe++) iron reacts with peroxides to produce free radicals, which are highly reactive and can damage DNA, proteins, lipids, and other cellular components. In that case, both free and bound iron lead to toxic cellular effects. Free iron generally occurs when iron levels exceed the capacity of transferrin to bind the iron. Transferrin is a glycoprotein that is responsible for iron homeostasis in vivo and maintains iron pool in the systemic circulation by binding with iron tightly but reversibly. Free circulating iron, (contrary to ferritin-bound stable iron when converted to oxyhydroxyl derivatives and hemosiderin) may initiate and propagate the production of free radicals, leading to lipid peroxidation. Moreover, oxidative stress arises due to a disturbed equilibrium between pro-oxidant/antioxidant homeostasis that further takes part in generation of Reactive Oxygen Species (ROS) and free radicals with potential toxicity to neuronal cells. The reason for neuronal cell hypersensitivity towards oxidative stress arises due to anatomic and metabolic factors. In the brain, various types of glial cells are present and these are involved in anatomic support and metabolic requirement (37). The endothelial cells surrounding these glial cells are less permeable for uptake of various molecules. In addition, glial cells in brain require more oxygen and glucose consumption to generate continuous ATP pool in vivo for normal functioning of brain with enhanced susceptibility to free radical injury.

The excessive amount of iron detected in MS patients by a variety of different MRI techniques, including SWI, and therapeutic strategies against iron accumulation in MS are becoming highly important research topics in this field.

Therefore, measurement of iron accumulation in the white matter (WM) and particularly in deep gray matter (DGM) of patients with MS may become a very important outcome for future clinical trials and targets of therapeutic intervention.

Although the effect of Rebif® 44 mcg on iron accumulation and iron mediated damage in MS patients is unknown, given its mechanism of action and its potent effect on the blood-brain-barrier breakdown recovery, it is an ideal drug candidate to test whether it can slow down iron accumulation in the WM and DGM in patients with MS.

The study will provide the following:

- An understanding of the effects of Rebif® on previously unexplored mechanisms (i.e., remyelination and iron deposition in the CNS)
- Elucidation of potential associations of above results with effects of Rebif® on pathogenic (T helper 17, Th17) immune cells
- Examine the association of above results with the ability of immune cells to produce neurotrophic factors
- Inform the design of future clinical trials that aim to incorporate these advanced technologies to investigate treatment outcomes
- Advance the science and medicine of Rebif®.

## Summary of Overall Risks and Benefits

Subjects will receive Rebif® at no cost for the duration of the trial. The use of Rebif® may not directly benefit subjects during the trial.

Common adverse events that occur in Rebif® treated patients include injection site reactions, injection site pain, flu-like symptoms, hepatic dysfunction and cytopenia. Skin rash, depressive symptoms and thyroid dysfunction have also been reported with Rebif® [(See Section 3.10)](#_Safety_Profile_of)

## Background of MS

Multiple sclerosis (MS) is a chronic, inflammatory, demyelinating disease of the central nervous system and is the most common cause of neurological disability in young adults. It is characterized by multi-focal recurrent attacks of neurological symptoms and signs with variable recovery. Eventually, the majority of patients develop a progressive clinical course (38-40)(39-41).

The exact cause of MS is unknown, although an autoimmune process has been implicated.

Genetic susceptibility plays a role in disease initiation, (42-43) (43) but currently unidentified environmental factors are also likely involved (44)

It is hypothesized that central nervous system (CNS) auto-reactive T cells are stimulated in the peripheral circulation to become active and proliferate. The expression of adhesion molecules on the surface of T cells permits adhesion to activated endothelial cells with subsequent migration of T cells into the CNS compartment. These cells upon interacting with CNS myelin antigens again proliferate, and initiate a pro-inflammatory cascade within the brain that results in either target-directed immune damage or bystander damage. Important cellular and humoral elements are T-lymphocytes, B-lymphocytes, dendritic cells, macrophages, microglial cells, metalloproteinases and pro-inflammatory cytokines, including interferon-gamma, and tumor necrosis factor-alpha (45-47)(46-47).

## Clinical Variants of MS

Four clinical forms of MS are recognized: primary progressive MS (PPMS), secondary progressive MS (SPMS), relapsing-remitting MS (RRMS) and progressive-relapsing MS (PRMS) (38-48). PPMS patients encompass about 10% of the MS population; their disease is characterized by slow and steady accumulation of neurological deficits from onset without superimposed events. A smaller percentage of patients will have a similar onset but with occasional clinical events (PRMS).

Patients with RRMS have acute exacerbations or clinical events with subsequent variable recovery (remission). At the onset of MS, 80 to 85% of patients will have the RR form of the disease. Fifty percent (50%) of RRMS patients will convert to SPMS within ten years of onset (49), with the peak time of conversion being at about eight years after the onset of the disease (38). The proportion of RRMS progressing to SPMS approaches 80% at twenty-five years. SPMS is characterized by the steady accumulation of significant and persistent neurological deficit with or without superimposed clinical events. Response to IFN-beta therapy may differ based on whether clinical relapses continue to occur in SPMS. The majority of patients with Expanded Disability Status Scores (EDSS) of 6.0 or higher have SPMS.

## Summary of Rebif® Pre-Clinical Trials

Rebif® pre-clinical trials have been reviewed and approved during the registration process and are briefly summarized below.

Rebif® was tested in toxicology studies of up to six months in duration in monkeys and three months in rats and caused no overt signs of toxicity. Rebif® has been shown to be neither mutagenic nor clastogenic. Rebif® has not been investigated for carcinogenicity. A study on embryo/fetal toxicity in monkeys showed no evidence of reproductive disturbances. Based on observations with other alpha and beta interferons, an increased risk of abortions cannot be excluded. No information is available on the effects of Rebif® on male fertility.

## Summary of Rebif® Clinical Trials

Rebif® has been tested in a series of studies in MS subjects at doses ranging from 22 mcg to 132 mcg weekly, with a dosing frequency ranging qw to tiw. The pivotal trial in RRMS was the 6789 (PRISMS) study (34;35;50;51), a double-blind, placebo controlled randomized trial of 22 mcg tiw or 44 mcg tiw Rebif®. The initial two-year study demonstrated that Rebif® at both doses significantly reduced clinical event rate (32% reduction for 44 mcg tiw relative to placebo, p<0.001), slowed disability progression (Hazard Ratio, [HR]=0.63, p=0.01), and reduced MRI lesion activity (77% reduction T2 active lesions, p<0.0001) and accumulation of new lesion burden (-3.8% compared to +11%, p<0.0001). Rebif® is the only disease modifying agent to have demonstrated efficacy on all four of these measures in RRMS.

A test of the importance of treatment regimen was performed in the 21125 (EVIDENCE) study (52), a direct comparative trial of INF-beta-1a 44 mcg tiw (Rebif®) vs. INF-beta-1a 30 mcg qw (Avonex®) in RRMS. This study demonstrated a 12% absolute difference (75% vs. 63%) in the proportion of subjects remaining clinical event-free over twenty-four weeks (primary outcome), which equates to a 19% relative reduction in the risk of clinical event over one year for Rebif® vs. Avonex® subjects (p<0.001). After forty-eight weeks, there was a 10% absolute difference (62% vs. 52%) in the proportion of subjects remaining clinical event-free, which also equates to a 19% relative reduction in the risk of clinical event over one year for Rebif® vs. Avonex® subjects (p=0.009). The time to first clinical event over forty-eight weeks was also significantly reduced with Rebif® (HR=0.70, p=0.003). The main secondary endpoint was based on serial brain MRI showing a 33% reduction in MRI combined unique active lesions for Rebif® relative to Avonex® (p<0.001) over twenty-four weeks, and 36% relative reduction in T2 lesion activity over forty-eight weeks (p<0.001). This study supports the concept of higher, more frequent IFN-beta dosing being more effective than low dose, low-frequency IFN-beta treatment.

## Safety Profile of Rebif® based on Clinical Trials

Rebif® has been well tolerated in all clinical pharmacology studies, even at high doses (up to 66 mcg/m2). In later phase clinical trials, Rebif® has been tested across a broad range of doses, for varying duration, and in different stages of MS disease. Dose testing has ranged from 22 mcg to 132 mcg weekly with frequency of administration being daily or thrice weekly. Subject age has ranged from 17 to 68 years.

Additional safety data from clinical trials in all indications studied, post-marketing surveillance and literature reports were compiled in the August 2001 Integrated Summary of Safety that summarized the safety of IFN-beta-1a across several MS and non-MS studies. The majority of exposure is for the specified indication of MS, principally RRMS. The data obtained from this population provide a good understanding of the safety profile of Rebif®.

These data show that, overall, Rebif® is well tolerated at the doses intended for use in the MS population, namely 44 mcg tiw administered by the sc route. The overall mortality rate on treatment is not greater than expected for untreated MS subjects nor is there an excess of serious adverse events on treatment compared to placebo.

The most common adverse events fall into four main categories: injection site reactions (ISRs), flu-like symptoms, hepatic dysfunction and cytopenia. With the exception of ISRs, these events usually occur during the first six months of therapy, are generally mild in severity and usually resolve spontaneously as Rebif® therapy is continued. They rarely require dose reduction or treatment interruption. Other common reactions observed during Rebif® therapy are skin rash, depressive symptoms, and thyroid dysfunction (manifested as hypo- or hyperthyroidism). Details are disclosed in the Rebif®Investigator’s Brochure.

# Trial Objectives

The purpose of this trial is to measure the effects of Rebif® 44 mcg sc tiw on a) remyelination/demyelination, b) lesion and brain volume, c) CNS iron deposition and d) immune status in subjects with RRMS using several MRI techniques.

## Primary Objective

The primary objective is to characterize the effect of Rebif® 44 mcg sc tiw on remyelination/demyelination using a voxel-wise magnetization transfer ratio (VW-MTR) dynamic mapping of normal appearing brain tissue (NABT) in subjects with RRMS over six months of treatment, and with reference to a group of healthy controls (HC).

## Secondary Objectives

Secondary objectives are to characterize the effect of Rebif® 44 mcg on:

- remyelination/demyelination using a VW-MTR dynamic mapping of lesions (T2, T1 & Gd) in RRMS subjects over six months of treatment, and with reference to HC
- brain volume using 3D-T1 imaging of whole brain and of gray matter (GM) in RRMS subjects over six months of treatment, and with reference to HC.
- CNS iron deposition using Susceptibility Weighted Imaging (SWI) of the deep gray matter (DGM), NABT and of the lesions in RRMS subjects over six months of treatment, and with reference to HC.
- Lesion volume (LV) using T2-LV, T1-LV and T1-Gd-LV imaging in RRMS subjects over six months of treatment vs. baseline.

Further secondary objectives are to assess the following immunologic, CNS, and clinical outcomes:

- Immune phenotype of T cells, and monocytes, with special focus on the levels of cytokines involved in the pathogenic Th17 pathway
- Immune cell production of neurotrophic factors, including nerve growth factor (NGF) and brain-derived neurotrophic factor (BDNF), in order to assess potential associations with remyelination, neurodegeneration, iron deposition or GM volumes
- Ferritin and transferrin level assessment, in order to assess the relationship of CNS iron deposition with ferritin levels and with transferrin levels
- Clinical relapses
- Safety evaluation
- Immunologic assessments will help establish associations with CNS effects and clinical outcomes.

# Investigational Plan

## Overall Trial Design and Plan

### Study Design

This is a twenty-four week, two arm, pilot trial to evaluate remyelination, neurodegeneration (brain atrophy), iron deposition in the CNS and immune status with RRMS patients treated with Rebif® 44 mcg sc three times a week (tiw) compared to a HC reference group.

### Primary and Secondary Endpoints

Primary Endpoint

The primary endpoints are the numbers of voxels (counted in milliliters) that change in VW-MTR value (both increase and decrease) from baseline to six-months in NABT of RRMS subjects treated with Rebif® as compared to NABT of HC.

Secondary Endpoints

The secondary MRI endpoints for RRMS subjects treated with Rebif® are:

- the number of voxels that increase in VW-MTR value at three months vs. baseline in NABT
- the increase and decrease in number of voxels from VW-MTR at three- and six-months vs. baseline in lesions
- brain volume using 3D-T1 imaging at three- and six-months vs. baseline in whole brain and GM
- the amount of iron deposition identified via SWI at three- and six-months vs. baseline in DGM, NABT and lesions
- lesion volume from T2-LV, T1-LV and T1-Gd-LV imaging at three- and six-months vs. baseline

The secondary immunology endpoints for RRMS subjects treated with Rebif® (six-months vs. baseline) are:

*Flow cytometry studies on CD4+ and CD8+ gated T-Cells:*

- intracellular IFN-gamma, IL-4, IL-17A, IL-17F, IL-21, IL-22 and IL-10 production
- nerve growth factor (NGF) and brain derived neurotropic factor (BDNF) secretion

*RT-PCR studies on:*

- Magnetic beads separated CD14+ monocytes
  - TLR3, 7 and 9;
  - cytokines IL-1α, IL-1β, IL-23p19, TGF-β, IL-12p70, IL-10, IL-27p28
  - cytokine receptors IL-1R1, IL-12Rβ, IL-23R, IL-21R, and IL-27R.
- Magnetic beads separated CD4+ and CD8+ T-cells
  - transcription factors T-bet, GATA3, ROR, IRF4 and FoxP3;
  - cytokines IFN-gamma, IL-4, IL-17A, IL-17F, IL-21, IL-22 and IL-10;
  - cytokine receptors IL-1R1, IL-23R, IL-21R, IL-12Rβ and IL-27R,
  - neurotrophic factors NGF and BDNF

Other secondary endpoints of the study examine potential associations of the effects of Rebif® in the CNS with peripheral effects on:

- number of clinical relapses
- time to first clinical relapse
- immune cell phenotype: related to CNS infiltration (Th17 cells)
- immune cell production of neurotrophic factors: related to remyelination or preservation of gray matter volume, and
- ferritin and transferrin levels: potentially associated with levels of CNS iron deposition.

### Safety Endpoints

The safety endpoints are to determine the incidence of adverse events following administration of study treatment with Rebif® over six months via electronic case report form (e-CRF) based adverse event collection.

### Study Subjects

It is estimated that fifty five subjects with RRMS will be screened, to achieve twenty-five intent to treat (ITT) subjects. In addition, 15 HC subjects will be enrolled as a reference group according to the same age range requirements and the same ratio of males to females as the RRMS subjects. It is estimated that the 40 subjects (25 RRMS and 15 HC) will be recruited at one center in the USA.

### Study Treatment with Medicinal Product

Subjects who satisfy the entry/eligibility criteria and sign an institutional review board approved Subject Information Sheet and Informed Consent Form will undergo treatment for twenty-four weeks with Rebif®. The dosing regimen complies with the product labeling of the currently marketed formulation of Rebif.

### Blinding and Randomization

The MRI analysis and immunologic studies will be rater-blinded. Neurologic exams will not be blinded.

### Overall Duration of the Study

Each eligible subject will undergo a screening evaluation, including informed consent, within fourteen days prior to entry into the trial. Study Day 1 is the first day a subject begins his/her injections of Rebif followed by a twenty-four week course of treatment for RRMS subjects; Study Day 1 is the day of the first MRI measurement for healthy controls. All subjects will have a follow-up telephone call four weeks after study treatment ends in order to monitor their status and well-being.

### Schedule of Assessments

Eligible subjects will undergo a screening assessment within fourteen days prior to entry into the trial. Thereafter, eligible subjects will return to the clinic for assessments on Study Day 1, Week 12, Week 24/Exit and Week 28 (telephone call). Refer to [(See Section 7.2)](#_Assessments_to_be) for a detailed listing of assessments to be performed at each clinic visit and the timing and frequency of those assessments.

The schedule of assessments for the RRMS subjects is illustrated below:

The schedule of assessments for the Healthy Control Group is illustrated below:

## Discussion of Trial Design

This is a twenty-four week, two arm, pilot trial to evaluate remyelination, neurodegeneration (brain atrophy), iron deposition in the CNS and immune status with RRMS patients treated with Rebif® 44 mcg sc tiw compared to a HC reference group.

Subjects who sign an institutional review board (IRB) approved Subject Information Sheet and Informed Consent Form will be enrolled with a scheduled study duration of twenty-four weeks plus a four-week, post-treatment telephone call to evaluate the safety and well-being of the study subjects.

During treatment, RRMS subjects will receive Rebif® 44 mcg sc tiw. MRI measurements for RRMS and HC subjects will be performed at Study Day 1, Week 12 and Week 24/Exit.

## Inclusion of Special Populations

Not applicable.

## Selection of Trial Population

### Inclusion Criteria

The following inclusion criteria must be fulfilled by RRMS subjects:

1. Male and female subjects, 18-65 years of age, inclusive, at the time of informed consent signature
2. RRMS diagnosed according to the McDonald criteria, treatment naïve or currently using any of the FDA-approved DMDs (excluding natalizumab (Tysabri®), mitoxantrone or Rebif®)
3. Have a disease duration for less than ten years
4. Be willing and able to comply with the study procedures for the duration of the trial
5. Have given written informed consent and signed Health Insurance Portability and Accountability Act (HIPAA) Authorization before any study-related activities are carried out
6. Female subjects must not be either pregnant or breast-feeding and must lack childbearing potential, as defined by either:
7. Being post-menopausal or surgically sterile, or using a highly effective method of contraception (defined as a method that results in a low failure rate (i.e. less than 1% per year) when used consistently and correctly, and includes for instance, implants, injectables, combined oral contraceptives, some intrauterine devices, sexual abstinence or vasectomized partner)
8. Female subjects of childbearing potential must have a negative serum pregnancy test at Screening and a negative urine pregnancy test at Study Day 1 to be included in the trial. A urine pregnancy test will also be done at the Week 24/Exit visit

*Note for subjects using a hormonal contraceptive method: No formal drug interaction studies have been carried out with Rebif®. As interferons have been reported to exert an inhibitory activity on hepatic microsomal enzymes, it is unlikely that the clearance of oral contraceptives would increase and result in decreased efficacy. In over 10,000 patient years of clinical trial experience with Rebif®, there has never been any indication of an interaction with oral contraceptives.

The following inclusion criteria must be fulfilled by the Healthy Control subjects:

1. Male and female subjects, 18-65 years of age, inclusive, at the time of informed consent signature
2. Be willing and able to comply with the study procedures for the duration of the trial
3. Have given written informed consent and signed Health Insurance Portability and Accountability Act (HIPAA) Authorization before any study-related activities are carried out
4. Female subjects must not be either pregnant or breast-feeding and must lack childbearing potential, as defined by either:
5. Being post-menopausal or surgically sterile, or using a highly effective method of contraception (defined as a method that results in a low failure rate (i.e. less than 1% per year) when used consistently and correctly, and includes for instance, implants, injectables, combined oral contraceptives, some intrauterine devices, sexual abstinence or vasectomised partner)
6. Female subjects of childbearing potential must have a negative serum pregnancy test at Screening and a negative urine pregnancy test at Study Day 1 to be included in the trial. A urine pregnancy test will also be done at the Week 24/Exit visit

### Exclusion Criteria

Subjects are not eligible for this trial if they fulfill any of the following exclusion criteria:

1. Have received treatment within three months prior to Screening with interferon-beta-1a (Rebif®), IVIG or plasmapheresis
2. Have received treatment within thirty days prior to screening with immunosuppressant agents (e.g. including but not limited to mitoxantrone, cyclophosphamide, cladribine, fludarabine, cyclosporine or total body irradiation) or any other concomitant immunomodulatory therapies (e.g., azathioprine, methotrexate, CellCept®, natalizumab, alemtuzumab/Campathand other immunomodulators/monoclonal agents)
3. Have had a relapse within thirty days prior to the Screening Visit
4. Have received steroid treatment within thirty days prior to the initial MRI scan date at Study Day 1
5. Have inadequate liver function, defined by a alanine aminotransferase (ALT) > 2.5x upper limit of normal (ULN), or alkaline phosphatase > 2.5x ULN, or total bilirubin > 1.5x ULN
6. Have inadequate bone marrow reserve, defined as a total white blood cell count < 3.0x 109/L, platelet count < 75x109/L, hemoglobin < 100g/L
7. Have complete transverse myelitis or simultaneous-onset bilateral optic neuritis
8. Have a history of alcohol or drug abuse
9. Have thyroid dysfunction
10. Have moderate to severe renal impairment
11. Have a major medical or psychiatric illness that in the opinion of the investigator creates undue risk to the subject or could affect compliance with the study protocol
12. Have a history of seizures not adequately controlled by treatment
13. Have serious or acute cardiac disease, such as uncontrolled dysrhythmias, uncontrolled angina pectoris, cardiomyopathy, or uncontrolled congestive heart failure
14. Have, in the opinion of the investigator, any visual, physical or cognitive impairment that would preclude the subject from complying with the study protocol
15. Have a known hypersensitivity or allergy to interferon-beta or any of the excipients
16. Have received an investigational drug or experimental procedure within the past thirty days
17. Are pregnant or attempting to conceive

The following exclusion criteria must be fulfilled by the Healthy Control subjects:

1. Have met any of the above noted criteria

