## Concomitant Medications and Therapies

### Permitted Medicines

Any concomitant medications (other than those excluded by the protocol) that are considered necessary for the subjects’ welfare and will not interfere with the Medicinal Product may be given at the Investigator’s discretion (e.g. analgesics for treatment of flu-like symptoms and corticosteroids for the treatment of relapses).

All such therapy will be recorded in the e-CRF from the time the Informed Consent Form is signed until the final post-treatment follow-up, along with medication name, dosage information, dates of administration, and reasons for use.

Concomitant medications for the following reasons should be documented in the e-CRF:

- MS related condition (e.g. pain, fatigue, bladder dysfunction, spasticity, etc.)
- Medical conditions reported in the subject’s Medical History (e.g. pain, headaches, depression, etc.)
- Prophylactic Use (e.g. flu-like symptoms, etc.)
- Self-medication (e.g. vitamins, nutritional supplements, herbal/natural products, etc.)

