# Trial Procedures and Assessments

## Schedule of Assessments

Prior to performing any trial assessments not part of the subject’s routine medical care, the Investigator will ensure that the subject or the subjects legal representative has provided written informed consent according to the procedure described in Section 9.2.

A screening log will be completed for all subjects who sign the Informed Consent Form (ICF) but do not subsequently enter the trial. Subjects will be identified by their initials and dates of birth, and reason(s) for exclusion from the trial will be recorded.

Please refer to [(see Appendix A)](#_Appendix_A_-) for a Schedule of Assessments to be performed during the conduct of this trial, as well as the frequency of testing over twenty-four weeks of treatment and the four-week, post-treatment telephone call.

In summary, subjects who sign an institutional review board approved ICF and who satisfy the eligibility criteria at Screening should then return to the clinic on Study Day 1, Week 12 and Week 24/Exit. The subjects will also receive a telephone call four weeks post-treatment to monitor their status and well-being.

Due to the workload of the clinic, as well as subjects’ own personal schedules, it is understood that there may be conflicts in subjects returning to the clinic on the exact day of their specified contacts. As such, a “window” of  seven days is permitted for subjects to be evaluated at each scheduled contact (Study Day 1, Week 12, Week 24 and Week 28 (telephone call).

Subjects will be asked to keep diary cards to collect information regarding treatment administration, concomitant medications, concomitant procedures and any adverse event(s) they experienced. This information will be discussed with each subject, and once confirmed by the Investigator or study personnel, it will be recorded in the appropriate e-CRF.

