### Screening Period

**RRMS Subjects**

The following information should be obtained at Screening (within 14 days prior to Study Day 1):

- A signed institutional review board (IRB) approved ICF and HIPAA Authorization (provide a copy to the subject, as well as retain a copy for the Investigator File).
- Medical History, including:
- Demographic data, including date of birth, gender and race
- Review of eligibility criteria
- Relevant medical history, including past and ongoing medical conditions related to MS
- For female subjects, birth control methods will be discussed and recorded
- Recording of adverse events and concomitant medications/procedures
- Physical examination unrelated to MS, including height, weight and vital signs [(see Section 7.2.6.1)](#_Physical_Examinations)
- Neurological assessment (full exam including EDSS) [(see Section 7.2.6.2)](#_Neurological_Assessments)
- Laboratory Assessments (Chemistry, Hematology, ferritin, transferrin, uric acid)
- A blood sample will be collected for analysis of thyroid function tests.
- Serum pregnancy test for female subjects of childbearing potential

**NOTE: Confirmation that a subject is not pregnant must be confirmed by a negative serum beta human chorionic gonadotropin (hCG) test within 14 days prior to Study Day 1 (the first day of dosing) and by a negative urine pregnancy test on Study Day 1.**

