**RRMS Subjects**

The following assessments must be performed:

- Re-confirmation that eligibility criteria are satisfied
- For female subjects of childbearing potential, a urine pregnancy test, to be performed locally at the study site
- Blood collection for Immunological Samples
- MRI
- Injection Training/Dispensing of Rebif®
- Provide each subject with a diary card and train on proper completion to record injection dates/times, concomitant medications/procedures and adverse events

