#### Neurological Assessments

A complete neurological assessment for RRMS subjects will be done at Screening and at the Week 24/Exit visit. The full exam will include mental status, cranial nerve status, motor exam, sensory exam, coordination and gait. The EDSS will only be scored for RRMS subjects at the screening visit.

If the initial examination is abnormal, and the abnormality occurred prior to informed consent, it should be captured in the medical history form of the e-CRF. If the neurological signs, including relapses, occurred or worsened after informed consent, including signs detected at the Week 24/Exit visit, they should be captured in the adverse event form of the e-CRF.

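### The relapse exclusion ends at Screening while the steroid exclusion runs to the Day 1 MRI, so a relapse in between that is not treated with steroids before the scan does not bar entry

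*Protocol*

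**What the plan says.** Two adjacent criteria in section 5.4.2 keep recent disease activity and its treatment away from the start of the trial, but they count back from different dates. Exclusion 3 applies to patients who "Have had a relapse within thirty days prior to the Screening Visit". Exclusion 4 applies to those who "Have received steroid treatment within thirty days prior to the initial MRI scan date at Study Day 1".

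The two dates can be two weeks apart. Section 7.2.1 for RRMS subjects reads: "The following information should be obtained at Screening (within 14 days prior to Study Day 1". Section 7.1 adds that a window of "seven days is permitted for subjects to be evaluated at each scheduled contact (Study Day 1, Week 12" and the later contacts.

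For RRMS subjects, section 7.2.2.1 lists as a Day 1 task: "Re-confirmation that eligibility criteria are satisfied". Appendix A marks eligibility at Screening only.

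Section 6.4.1 names, among permitted treatments, "corticosteroids for the treatment of relapses". On relapses after consent, section 7.2.6.2 says: "If the neurological signs, including relapses, occurred or worsened after informed consent, including signs detected at the Week 24/Exit visit, they should be captured" on the adverse event form. It does not link them to entry.

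**The concern.** The steroid criterion shows that the protocol wants the baseline scan protected, but the relapse criterion stops short of that scan. The result runs against its apparent purpose: an older relapse excludes a patient and a fresher one need not.

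The longitudinal MRI endpoints are changes from the Day 1 scan, and the immunology endpoints are changes from the Day 1 blood sample. A patient assessed during an untreated relapse may start with active lesions, low lesion MTR and an acute immune profile. Natural recovery would then appear as increasing-MTR voxels, falling Gd or T2 lesion volume, or a shift in cytokines. The protocol interprets rising MTR as remyelination, so recovery in these measures would tend to favour the drug. Section 8.2 confirms a single treated RRMS group, and healthy controls cannot show recovery from a relapse.

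**Working it through.** The plan has no figure of its own to reproduce here: section 8.1 bases the sample size on clinical considerations. The check therefore compares the criteria, then estimates scale.

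**1. Timeline.** Put the Day 1 scan at day 0 and Screening at its earliest, day −14.
- Exclusion 3 covers day −44 to day −14.
- Exclusion 4 covers steroid use from day −30 to day 0.
- A relapse 29 days before Screening falls on day −43 and excludes.
- A relapse the day after Screening falls on day −13 and is outside exclusion 3. It excludes only if steroids are given before the scan.
- The interval not covered by the relapse criterion is up to 14 days. With both look-backs ending at the scan it would be 0.

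**2. Does anything else close the gap?**
- Day 1 re-confirmation (7.2.2.1): exclusion 3 still reads as satisfied, because its window ended at Screening.
- Exceptions (5.4.3): this section only allows criteria to be relaxed.
- Withdrawal (5.4.5): this concerns leaving treatment, and does not list relapse.
- Recording of relapses (7.2.6.2 and Reporting of MS Relapses): capture only, no bar to entry.

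**3. Which endpoints are exposed?** The MRI Analysis section overlays lesion maps to separate NABT from T2, T1 and Gd lesions, so focal recovery falls mainly on the secondary lesion MTR and lesion volume endpoints. Healthy controls receive no gadolinium (MRI Acquisition) and give no Week 24 immunology sample (7.2.5). Changes in Gd lesions and immunology are therefore judged within the RRMS group alone, where section 8.4.2 provides a signed-rank test over time.

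**4. Scale, on an assumption.** Section 3.9 quotes 75% and 63% event-free at 24 weeks (168 days) in two treated arms of another trial. As constant hazards, h = −ln(S)/168 per day. Over 14 days, p = 1 − exp(−14h). The expected count in 25 is 25p, and the chance of at least one is 1 − (1 − p)^25. Two assumed annual rates bracket these.

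| Rate used | h per day | p | 25p | At least one |
|---|---|---|---|---|
| 75% event-free (about 0.63 per year) | 0.2877/168 = 0.00171 | 0.0237 | 0.59 | 45% |
| 63% event-free (about 1.00 per year) | 0.4620/168 = 0.00275 | 0.0378 | 0.94 | 62% |
| 0.5 per year, assumed | 0.5/365.25 = 0.00137 | 0.0190 | 0.47 | 38% |
| 1.5 per year, assumed | 1.5/365.25 = 0.00411 | 0.0559 | 1.40 | 76% |

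At each rate these are upper bounds. They use the full 14 days for every patient and are taken before removing those whom exclusion 4 catches. If half were given steroids before the scan (an assumption), the two cited rates would leave 0.59/2 = 0.30 to 0.94/2 = 0.47 patients. One patient is 1/25 = 4% of the group.

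**The case against.** The strongest reply is that the gap is narrow. Exclusion 4 removes any patient given steroids before the scan, and the protocol itself names steroids as relapse treatment. What remains is a relapse within about two weeks that is untreated, or treated only after the scan. That is correct and limits the point.

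Other objections that stand:
- The hazards come from treated patients in another trial, and nothing shows that they apply here.
- The rank-based tests limit one patient's influence, although means are also reported.
- Relapses are recorded, so affected patients can be identified, and section 8.4.2 allows exploratory covariates for the primary endpoint. This makes the problem visible but does not prevent it.
- The root cause is the missing untreated RRMS group. Relapses more than 30 days before the scan, and clinically silent lesions, raise the same question.

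Three stronger readings are tempting but unsupported. A reader might infer that every patient relapsing after Screening stays eligible; exclusion 4 contradicts this. A reader might add the seven-day window to the 14 days and call the gap 21 days. However, section 5.1.7 defines Study Day 1 for RRMS subjects as the first day of injections, and section 7.2.1 counts the 14 days back from it, so a visit window need not lengthen them. A reader might also infer that the primary result is biased, but the documents do not show that recovery reaches NABT.

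**Conclusion.** The mismatch is real on the plain wording. Exclusion 3 ends at Screening, exclusion 4 ends at the baseline scan, and no other provision bars a patient who relapses in between without steroids before the scan.

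At the cited rates this concerns at most 0.6 to 0.9 of 25 patients over 14 days, with a 45% to 62% chance of at least one, and fewer once exclusion 4 has acted. These figures assume constant hazards carried over from on-treatment patients elsewhere. The documents do not quantify recovery, so the size of any bias is unknown. The exposure lies mainly in the secondary lesion MTR, Gd and T2 lesion volume and immunology endpoints. No sample size, power or alpha figure changes. It is a modest point, worth correcting because the correction is cheap and the within-group comparison has no untreated RRMS control.

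**What to change.** Reconcile exclusions 3 and 4 so that the relapse look-back, like the steroid look-back, runs to the initial MRI scan on Study Day 1, keeping the stated thirty days. Have the Day 1 re-confirmation in section 7.2.2.1 check it explicitly, and add that check to Appendix A. Reconcile the 14-day screening limit in section 7.2.1 with the seven-day window for Study Day 1 in section 7.1, so that the longest permitted interval is stated once.

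The cost is a short amendment to the criterion and the schedule. At the cited rates, about one patient at most would become ineligible on Day 1. The change does not address relapses more than 30 days before the scan, nor does it supply the missing untreated comparison.
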